## Abstract

**Background:**

Sepsis is as a life-threatening organ dysfunction caused by a dysregulated host response to an infection. The mortality of sepsis and particular of septic shock is very high. Treatment mostly focuses on infection control but a specific intervention that targets the underlying pathological host response is lacking to the present time.

The investigators hypothesize that early therapeutic plasma exchange (TPE) will dampen the maladaptive host response by removing injurious mediators thereby limiting organ dysfunction and improving survival in patients with septic shock. Although small prospective studies demonstrated rapid hemodynamic stabilization under TPE, no adequately powered randomized clinical trial has investigated hard outcomes.

**Methods:**

This is a randomized, prospective, multicenter, open-label, controlled, parallel-group interventional trial to test the adjunctive effect of TPE in patients with early septic shock. Patients with a refractory (defined as norepinephrine (NE) ≥ 0.4 μg/kg/min ≥ 30 min OR NE 0.3 μg/kg/min + vasopressin) and early (shock onset < 24 h) septic shock will be included. The intervention is a standard TPE with donor fresh frozen plasma (1.2 × individual plasma volume) performed within 6 h after randomization and will be compared to a standard of care (SOC) control arm. The primary endpoint is 28 days mortality for which the power analysis revealed a group size of 137 / arm (*n* = 274) to demonstrate a benefit of 15%. The key secondary objective will be to compare the extent of organ failure indicated by mean SOFA over the first 7 days as well as organ support-free days until day 28 following randomization. Besides numerous biological secondary, safety endpoints such as incidence of bleeding, allergic reactions, transfusion associated lung injury, severe thrombocytopenia, and other severe adverse events will be assessed during the first 7 days. For exploratory scientific analyses, biomaterial will be acquired longitudinally and multiple predefined scientific subprojects are planned. This study is an investigator-initiated trial supported by the German Research Foundation (DFG, DA 1209/7–1), in which 26 different centers in Germany, Switzerland, and Austria will participate over a duration of 33 months.

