### Sample size

The primary aim of the study is to demonstrate superiority of SOC + TPE compared to SOC alone with regard to the primary endpoint 28-day mortality. In a prospective, monocentric, non-controlled pilot study of the TPE treatment in patients with septic shock, the observed 28-day mortality rate was 65%, while the predicted mortality rate using the APACHE-II-score was as high as 91% [10]. Meanwhile, two randomized clinical trials have been conducted. In one (small, *n* = 20 vs 20) randomized control trial, the observed mortality rate of the TPE-treated patients was 40% in contrast to 50% in the control group, resulting in a risk difference of − 10% with a 95% CI of [− 0,41;0,21] [14]. In another randomized control trial, the observed mortality rate of the treated patients was 33.3 and 53.8% in the control group, resulting in a risk difference of − 21% with a 95% CI of [− 0.39; − 0.02] [8]. For sample size calculation, we considered the two RCTs only and combined the outcome in a meta-analysis. The treatment procedures were similar, and the two trials are very homogeneous (I2 of 0%). The meta-analysis resulted in a risk difference of − 18% with a 95% CI of [− 0.34; − 0.02]. This risk difference was used in the sample size calculation. Sample size calculation was done for a two-group continuity corrected chi-square test (Query Advisor 8.7.1.0). To detect a reduction in 28-day mortality rate from 60 to 42% in the experimental group with a two-sided type I error rate of 5% and a power of 80%, at least 131 patients per group are required. Thus, the total sample size to detect the expected effect on the 28-day mortality is 262 patients. Stratification for sex, center, pulmonary focus of infection (yes/no), and lactate (< / ≥ 4.5 mmol/) at randomization is assumed to increase power of the statistical test. Considering a drop-out rate of 5%, a total of 274 patients will be assigned to the trial, i.e., recruited.

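### The abstract ties 137 per arm to a 15% mortality benefit, but the trial was sized for 18 points; for 15 points the power is about 66%, not 80%

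*Protocol article*

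**What the plan says.** The Methods paragraph of the abstract says that "the power analysis revealed a group size of 137 / arm" (n = 274) in order "to demonstrate a benefit of 15" percent. It gives no control rate and no power, and does not say whether the 15% is absolute or relative.

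The Sample size section pools two randomised trials to a risk difference of −18% and says: "This risk difference was used in the sample size calculation". The target is then given as event rates: "To detect a reduction in 28-day mortality rate from 60 to 42% in the experimental group". Alpha is 5%, two-sided, and the planned power is 80%. The stated result is 131 patients per group, 262 in total, raised to 274 for 5% drop-out. The test assumed is also stated: "Sample size calculation was done for a two-group continuity corrected chi-square test".

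No calculation for a 15% benefit appears anywhere in the article.

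**The concern.** One sample size is attached to two different target effects on the primary endpoint. The required number grows roughly with the inverse square of the difference, so 15 and 18 points are not interchangeable and the gap is not rounding. A reader of the abstract alone would believe the trial was built to detect a 15-point benefit. If it has materially less than the planned power there, the abstract overstates its sensitivity, and a non-significant result could be taken as stronger evidence against a 15-point benefit than it is. The article plans no interim analysis and describes no sample size re-estimation, so nothing in the design would later make up the difference.

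**Working it through.** **Inputs (Sample size section):** control mortality 60%, TPE mortality 42%, two-sided α = 5%, power 80%, continuity-corrected chi-square test, 5% drop-out. Allocation is 1:1. The abstract gives no control rate, so 60% is carried over as an assumption and varied below.

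**Formulas.** With d = p1 − p2 and p̄ = (p1 + p2)/2:

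- Uncorrected n per arm: n0 = [1.960·√(2p̄(1−p̄)) + 0.8416·√(p1(1−p1) + p2(1−p2))]² / d²
- Continuity-corrected: n = (n0/4)·[1 + √(1 + 4/(n0·d))]²
- Corrected power at n per arm: Φ{(d − 1/n − 1.960·s0)/s1}, where s0 = √(2p̄(1−p̄)/n) and s1 = √((p1(1−p1) + p2(1−p2))/n)

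**Step 1: reproduce the plan's figure, 60% vs 42%.**

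- n0 = (1.3856 + 0.5853)²/0.0324 = 119.9
- Corrected n = 130.8, so 131 per arm and 262 in total, as stated.
- Power at 131: Φ{(0.18 − 0.0076 − 0.1211)/0.0608} = Φ(0.844) = 80.1%. At 137 it is 82.0%.
- Drop-out: 262/0.95 = 275.8 against the stated 274, a small difference that does not matter here.

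The Sample size section is therefore consistent with an 18-point target.

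**Step 2: the abstract's target as 15 points, 60% vs 45%.**

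- n0 = (1.3842 + 0.5876)²/0.0225 = 172.8
- Corrected n = 185.9, so 186 per arm and 372 in total; 372/0.95 = 391.6, so about 392 with 5% drop-out.
- Power at 137: Φ{(0.15 − 0.0073 − 0.1183)/0.0597} = Φ(0.410) = 65.9%
- Power at 131: Φ{(0.15 − 0.0076 − 0.1209)/0.0610} = Φ(0.351) = 63.7%

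**Step 3: how far the answer depends on method and assumptions.**

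| Per arm | Method | 60 vs 42% | 60 vs 45% |
|---|---|---|---|
| 131 | corrected, normal approximation | 80.1% | 63.7% |
| 131 | corrected, exact enumeration | 81.3% | 65.4% |
| 131 | uncorrected, normal approximation | 83.4% | 68.3% |
| 137 | corrected, normal approximation | 82.0% | 65.9% |
| 137 | corrected, exact enumeration | 81.1% | 64.8% |
| 137 | uncorrected, normal approximation | 85.0% | 70.3% |

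- *Control rate.* For a 15-point difference from control rates of 50% to 65%, corrected power at 137 per arm is 65.8% to 66.8%. It reaches 80% only near a control rate of 30% (134 per arm needed), well below the 50% and 53.8% seen in the control arms of the two trials the section cites.
- *Relative reading.* A 15% relative reduction is 60% to 51%. It would need 500 per arm and has about 28% power at 137. The planned effect is a relative reduction of 18/60 = 30%.
- *Drop-out allowance.* Using all 137 per arm does not bring the target down to 15. The difference from 60% detectable with 80% power is then about 17.6 points (16.8 uncorrected).

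**Step 4: the group size.** The abstract presents 137 per arm as the output of the power analysis. The Sample size section gives 131 as that output; 137 is 274/2, after the drop-out allowance.

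**The case against.** The strongest reply is that this is one clause in an abstract. The Sample size section governs, is complete and reproduces; no endpoint, analysis, decision rule or recruitment number depends on the 15%. The abstract does not itself claim 80% power, so the trial is not underpowered against its own plan. That is right: the defect is a misreported target effect, not a sizing error. It still needs correcting, because the target effect on the primary endpoint is a core design figure and the abstract is where most readers meet it.

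The power figures above are for an unadjusted test, whereas the primary analysis is a logistic regression adjusted for the stratification factors, which the protocol assumes will raise power. This also stands in part: 66% lies toward the lower end of a 64–70% range, and adjustment could add something. But the protocol does not quantify that gain, and it would apply to the 18-point target as well, so it does not reconcile the two statements.

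Finally, inference will rest on a confidence interval, which shows what the data exclude whatever the abstract says. That limits the harm for a careful reader, but does not make the abstract's statement true. Reporting the recruitment figure of 137 would be unremarkable alone; here it is described as the result of the power analysis, which it is not.

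**Conclusion.** The concern holds. The abstract's 15% contradicts the only sample size calculation in the document, and no reading of it, absolute or relative, fits 137 per arm. The calculation supports an 18-point reduction (60% to 42%). For 15 points the power is about 66% at 137 per arm under the protocol's own test, and between 64% and 70% across the unadjusted variants at a 60% control rate; it is below 80% in all of them. A true 15-point benefit would thus be missed about one time in three. These figures assume a control rate near 60% (the result barely moves between 50% and 65%). The 137-per-arm figures also assume that every randomised patient is analysed, which fits the rule that unknown vital status counts as death. The error lies in the abstract, not in the Sample size section.

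**What to change.** Reword the abstract to say: 131 patients per arm give 80% power to detect an absolute reduction in 28-day mortality of 18 percentage points (60% to 42%, two-sided 5%); 137 per arm (n = 274) will be recruited to allow for drop-out. Check whether any other trial text, such as registry, consent or DSMB material, repeats the 15% figure, and correct it there too; those texts are not at hand, so this is a precaution.

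It would also help to add one sentence to the Sample size section: power for a 15-point reduction is about 64–66% with the continuity-corrected test, and up to about 70% without the correction, before any gain from covariate adjustment.

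The cost is wording only. The sample size does not change, though the stated detectable effect becomes less favourable. If the sponsor in fact intends 15 points as the target, rewording is not enough: the same method then gives 186 per arm, 372 in total, or about 392 with 5% drop-out.

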**Discussion:**

This trial has substantial clinical relevance as it evaluates a promising adjunctive treatment option in refractory septic shock patients suffering from an extraordinary high mortality. A positive trial result could change the current standard of care for this septic subgroup. The results of this study will be disseminated through presentations at international congresses, workshops, and peer-reviewed publications.

**Trial registration:**

ClinicalTrials.gov NCT05726825, Registered on 14 February 2023.

## Trial status

The current version of the study protocol described in the manuscript is Version 1.2, January 2023. The trial was registered at ClinicalTrials.gov (NCT05726825, date of registration: February 14, 2023, last update: February 14, 2023). No patient has yet been recruited. Anticipated start of trial recruitment will be in June 2023. Approximate end of recruitment will be May 2025.

## Introduction

### Background and rationale

Sepsis is defined as a life-threatening organ dysfunction caused by a dysregulated host response to an infection [1]; in septic shock, profound circulatory, cellular, and metabolic abnormalities are associated with high mortality [2]. Sepsis is a major healthcare problem, affecting millions of individuals around the world each year. Its incidence appears to be rising, and the mortality caused by septic shock remains extraordinarily high [3]. Septic shock patients do not die from their infection per se but rather from multiple organ failure caused by an overwhelming host response. In fact, this essential mechanism has been implemented as a key part of the 2016 sepsis definition (SEPSIS-3) [1]. Despite tremendous efforts during the last decades, innovative approaches targeting this fundamental hallmark of the disease, thereby reducing organ dysfunction, are still lacking [4]. Undoubtedly, there is an unmet medical need to expand the current standard of care for these patients by a more specific intervention.

The investigators hypothesize that early therapeutic plasma exchange (TPE) in the most severely ill individuals with septic shock will dampen the maladaptive host response by removing injurious mediators thereby limiting organ dysfunction [5, 6]. Due to its non-selective nature in removing injurious mediators (virtually all pro-inflammatory cytokines, coagulatory molecules and growth factors including permeability mediators and glycocalyx sheddases, etc.), TPE might be more efficient than pharmacological blockade of single components of this process. Moreover, it might also reduce the molecular triggers of inflammation by removing pathogen associated molecular patterns (PAMPs) such as lipopolysaccharides and damage associated molecular patterns (DAMPs) that are released by pathogens or injured host cells.

A meta-analysis from 2014 found four single-center randomized controlled trials (RCTs) that analyzed TPE in sepsis. In adults, TPE was associated with a reduced mortality (relative risk 0.63) [7]. The largest of those trials showed a trend towards improved survival [8]. However, this study was underpowered and had included a heterogeneous group in terms of disease severity (e.g., less 60% with shock). Many of their patients might have recovered anyways with standard treatment. Of note, the American Society For Apheresis (ASFA) grades “sepsis with multi-organ dysfunction” as potential 2B, category III indication for TPE (= optimum role not established, decision should be individualized) [9]**.**

The investigators performed a single-center prospective pilot study to analyze safety, feasibility, and primary efficacy endpoints in preparation for the here proposed multicenter RCT in a septic shock cohort [10] with similar inclusion criteria (i.e., early and severe septic shock). TPE was found safe and feasible, and we observed positive effects with regard to secondary efficacy endpoints, e.g., rapid reduction of NE requirement [10]. A subsequentially conducted randomized controlled bi-center trial (Hannover and Bonn) in 20 vs 20 patients found a highly significant reduction in NE in the treatment group within 6 h compared to the SOC group (2). In 2020, Keith and co-workers additionally reported in a propensity score matched observational trial of septic shock patients treated with TPE a significantly better survival rate [11]. Incorporating these novel data from the last 2 years in a fixed effect meta-analysis, the investigators found a risk ratio for mortality of 1.49 [1.15; 1.94] favoring plasma exchange (unpublished data).

### Objective

As no adequately powered trial has been performed, the definite role of TPE as an adjunctive treatment option in septic shock remains unclear. Therefore, the objective of the here proposed study is to demonstrate that additive early TPE compared to SOC reduces the 28-day mortality in patients with septic shock.

### Trial design

This is a randomized, prospective, multicenter, open-label, controlled, parallel-group interventional trial to test superiority of adjunctive TPE over standard of care treatment in patients with early septic shock. The study will have two arms: a treatment arm, in which patients receive a singular session of TPE using fresh frozen plasma (FFP) as replacement fluid (optional second TPE session after 24 h possible, see below) and a control arm, in which patients are treated with the current SOC (Fig. 1). The primary endpoint is 28 days mortality. Study participants will be followed up at 90 days and 1 year following study inclusion. This study is an investigator-initiated trial funded by the German Research Foundation (DFG, DA 1209/7–1).

**Fig. 1 Fig1:**
[figure not shown]
Trial structure

## Methods

### Study setting

A total of 274 septic shock patients (1:1 randomization) will be included in approximately 26 study centers. The study is planned at intensive care units (ICUs) of the following medical facilities in Germany, Switzerland, and Austria (EXCHANGE-2 study group):

In Germany: Hannover Medical School, Medical Intensive Care, Hannover Medical School, Anesthesiology Intensive Care, University Hospital Bonn (UKB), University Hospital Charite, Hospital St. Joseph, Berlin, Hospital Braunschweig, Reinkenheide Hospital, Bremerhaven, University Hospital Erlangen, University Hospital Essen, University Hospital Hamburg Eppendorf, Hospital Hannover Region, University Hospital Halle, University Hospital Heidelberg, University Hospital Jena, University Hospital Kiel Schleswig–Holstein (UKSH), Kiel, University Hospital Cologne, Hospital Cologne-Meerheim, Hospital Magdeburg, University Hospital Muenster Anesthesiology, University Hospital Rostock, Marienhospital Stuttgart, Stuttgart, Germany, University Hospital Munich (TU), University Hospital Munich (TU)**,** University Hospital Zurich (Switzerland), Inselspital Bern (Switzerland), Landeskrankenhaus Innsbruck (Austria) and “Allgemeines Krankenhaus der Stadt Wien,” Vienna (Austria).

### Eligibility criteria

Patients have to fulfill all of the following inclusion criteria to be eligible for participation in the study:Onset of septic shock within < 24 h (SEPSIS-3 definition) ANDNorepinephrine (NE) dose of ≥ 0.4 μg/kg/min ≥ 30 min OR≥ 0.3 μg/kg/min + vasopressin (any dose)for ≥ 30 min (target mean arterial pressure (MAP) ≥ 65 mmHg) despite adequatecrystalloid fluid resuscitation of ≥ 30 ml/kg body weight ANDEstablished vascular access suitable for plasma exchange independent of study inclusion (due to established indication of renal replacement therapy (RRT), expected need for RRT within the next 48 h or other medical reasons as assessed by treating physician team)

#### Patients are excluded from participation in the trial if they meet one of the exclusion criteria

Age < 18 years and > 80 yearsUrogenital focus of infectionHeparin-induced thrombocytopenia (HIT)PregnancyKnown history of transfusion reactionsVasopressor requirement due to non-septic shock (e.g. cardiogenic shock)Ineligible for intensive care without restrictions or limitations

### Who will take informed consent

A stratified randomization approach will be used. Patients who meet the respective inclusion criteria and who or whose proxy or legal representative give written informed consent to participate will be included. If the legal representative is not available to give written consent at place, a telephone-based education of the legal representative will be performed and a consultant physician (not involved in the patient’s care) will sign the consent form on behalf. The written consent of the legal representative will then be obtained in retrospect as soon as possible. Once a patient meets the criteria of early (< 24 h) and severe septic shock (NE dose ≥ 0.4 μg/kg/min or NE dose of ≥ 0.3 μg/kg/min + vasopressin), the patient will be randomized. Permuted block randomization with variable block length and stratified by center, sex (m/f), pulmonary focus of infection (yes/no), and baseline (at screening) lactate (< 4.5/ ≥ 4.5 mmol/l) will be used to allocate patients to the intervention and the control groups in a 1:1 ratio. Randomization will be conducted centrally using a web-based approach (eCFR).

The investigator is responsible for obtaining patient’s/legal representative’s written informed consent after adequate explanation of the aim, study assessments, potential risks and benefits, and consequences of the study as well as alternative treatment options. If patients are incapable of giving consent due to unconsciousness, informed consent may be given by a legal representative who has been designated by the local court. After retrieval of capacity for informed consent, patients have to be informed about study-specific interventions that have already been done and about the treatments that are planned in the future.

The patient information/informed consent form and the consent form for acquiring biomaterial have to be signed in duplicate by the patient/legal representative and the investigator. One document will be given to the patient/legal representative, the other one remains in the trial investigator file (TIF) at the trial site. No study procedures are allowed to be conducted until patient’s/legal representative written informed consent has been obtained. The patient information/informed consent form has to be revised whenever important new information becomes available that may be relevant to the subject’s consent. The patients have to be informed and asked to give their consent to continue study participation by signing the updated form. Participation in this clinical trial is voluntary. Withdrawal from the trial at any time and for any reason is without any disadvantages to the patient’s further treatment. In order to enable an unbiased assessment of the primary endpoint, and given that informed consent from the patient/ legal representative is required in order for the patient to be included into the trial, the endpoint of mortality at 28 days will be obtained from all patients and analyzed in the form of an intention-to-treat analysis, indiscriminate of a withdrawal of consent at a later point. In case of a patient’s withdrawal of informed consent, all study data collected up to the point of consent withdrawal will be anonymized and employed for further analyses solely in its anonymized form. However, in cases for which data from formally withdrawn patients is of relevance for the security assessment of this trial, anonymization will be delayed and only performed at an unspecified later point in time when security clearance is given by the trial responsible.

### Interventions

#### Study procedure (control arm): standard of care treatment

Subjects enrolled in this study will be treated in accordance with evidence-based international guidelines for the management of sepsis [1, 12]. Explicitly, participation of a center in this study indicates conformity with the tenets of treatment outlined in the 2021 Surviving Sepsis Campaign [12]. Among other therapeutic strategies, this implies that basic hemodynamic targets such as a MAP > 65 mmHg, HR < 120 BPM, SaO_2_ > 94%, and Hb > 7 g/dl will be employed, and that norepinephrine and balanced crystalloids will be administered as the first vasopressor and fluid of choice, respectively. Use of dynamic preload parameters to guide fluid resuscitation is strongly encouraged. Furthermore, antibiotics will be administered according to local standards for as long as necessary indiscriminate of the duration of the study. Antibiotic stewardship, including daily assessment of antibiotic escalation and de-escalation, is strongly encouraged. Additionally, patients who conform to the definition of ARDS will be ventilated with a low tidal volume ventilation strategy (6 ml/kg IBW) and those with a moderate-to-severe ARDS will be positioned in prone position for more than 12 h daily. As recommended for patients in refractory septic shock, hydrocortisone 4 × 50 mg/day (or 200 mg/day as continuous infusion) should be given to all patients until shock resolution and for max. 7 days. No other experimental adjunctive therapies for septic shock, including immunoglobulins and/or hemoperfusion, will be permitted.

